Duration of symptoms, underlying diagnosis and pre-procedure breathlessness were common factors identified by our clinician survey as being important in estimating how quickly pleural fluid will recur. Current treatment may reduce how quickly an effusion recurs. The co-morbidities specified are all associated with the production of pleural fluid, which may increase the rate of reaccumulation (despite the main cause being malignancy). Pre-procedure size of effusion was identified on two previous retrospective cohort studies as being associated with the need for a further pleural procedure, and we are measuring this in three ways (on X-ray, US and volume fluid drained). Septations are fibrin or collagen walls that develop within the effusion and impair drainage, and therefore may influence rate of reaccumulation. Non-expandable lung is defined as failure of the lung to re-expand following therapeutic aspiration and will be visible on the post-procedure CXR. It is associated with significant negative pressure within the pleural space, which may drive rapid pleural fluid reaccumulation. pH, LDH and cytology have been identified in previous studies as being associated with the need for a further pleural procedure. Total protein determines whether an effusion is an exudate or transudate and therefore is an important variable determining the mechanism of pleural fluid production. LDH has been identified as a variable associated with poor prognosis in patients with MPE. Haemoglobin, neutrophil: leukocyte ratio and C reactive protein have been shown to be associated with prognosis in patients with MPE. NT-proBNP is a measure of cardiac function and eGFR is a measure of renal function, so these variables may affect pleural fluid reaccumulation. High pleural fluid pressures may be associated with a strong drive to produce pleural fluid and hence rapid reaccumulation. These candidate biomarkers will be assessed to see which are appropriate for further analysis, based on our ability to detect variability within these measurements. If required, principal component analysis will be used to reduce the number of variables to eight for further analysis.

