**Sample size and analysis plan**
*

Based on our feasibility data, we estimate we need to recruit 200 patients to have complete data available on 150 patients. The main reason for this is that approximately 20% of patients will turn out not to have MPE and therefore will not be eligible for inclusion in the final analysis. The primary outcome measure is at one week and is part of standard clinical care and therefore we anticipate that loss to follow-up, withdrawal rates and missing data will be minimal based on our feasibility data and previous trial experience. A further validation cohort of 40 patients will be recruited subsequently. Follow-up will be either by review of available medical records, telephone or clinical appointment (if patient is coming up to hospital anyway) at 30 days and three months.

A sample size of 150 participants would allow us to have a shrinkage factor of 0.95, which is above the recommended 0.9, assuming an R
^2^ value of 0.5 and 8 parameters in the model. It would also allow the estimated R
^2^ value to be within recommended limits of 0.05 of the true R
^2^ value. It would allow the estimation of residual standard deviation to be within 13%. Although this is above the recommended 10%, we believe that it is still clinically meaningful. It also allows the estimation of the mean outcome to within +/- 1.5%, which is sufficiently precise to be clinically useful, assuming an overall mean of 14 and an SD of 13. This represents 18.75 individuals per variable, which is within the traditional 10–20 individuals per variable rule-of-thumb. The analysis will be based on traditional regression methods and follow the Transparent reporting of a multivariable prediction model for individual prognosis or diagnosis (TRIPOD) statement
^
16
^. An outline of the analysis is as follows:

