1.Initial screening of potential predictor variables to ensure that there is sufficient variation in them and that they are not missing at an unreasonably high level. For example, if a categorical variable does not have >5% of participants in any category; or if a continuous variable does not cover a broad enough range. After the initial screening, if appropriate data reduction techniques such as principal component analysis will be undertaken to reduce the number of variables to a reasonable amount.2.Model selection will then be undertaken using variable selection such as backwards elimination. Continuous covariates will be checked for non-linear relationships using splines.3.Once an appropriate model has been selected, the optimism and internal validation will be estimated using a non-parametric bootstrap approach. If overfitting if found to be an issue, then penalised regression (Lasso or Ridge regression) will be used to reduce the amount of overfitting.4.Once the final prediction model has been estimated, its properties such as discrimination by the estimation of the R
^2^ and calibration by plotting the observed outcome against the predicted outcome will be explored. If there is a large number of participants excluded due to missing predictor variables, then the sensitivity of the final prediction model to missing data will be assessed using multiple imputation.

*

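### Shrinkage is conditional on a bootstrap run after variable selection, and no optimism correction is stated for a penalised refit

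*Protocol article*

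**What the plan says.** The protocol article's outline, under Sample size and analysis plan, runs in this order.

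- **Step 1:** screening, then, if appropriate, "data reduction techniques such as principal component analysis will be undertaken to reduce the number of variables to a reasonable amount". The Objectives section is more specific but also conditional: if required, "principal component analysis will be used to reduce the number of variables to eight for further analysis".
- **Step 2:** "Model selection will then be undertaken using variable selection such as backwards elimination". No elimination criterion is given.
- **Step 3:** after a model has been selected, a non-parametric bootstrap estimates optimism. Then: "If overfitting if found to be an issue, then penalised regression (Lasso or Ridge regression) will be used to reduce the amount of overfitting". The outline does not say what counts as an issue, or whether elimination is repeated in each resample.
- **Step 4:** "Once the final prediction model has been estimated, its properties such as discrimination by the estimation of the R"² and a calibration plot are examined. No optimism correction is stated at this step.

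The same section justifies the sample size by expected shrinkage: "A sample size of 150 participants would allow us to have a shrinkage factor of 0.95, which is above the recommended 0.9", assuming an R² "value of 0.5 and 8 parameters in the model". A separate Phase 2 cohort of 40 patients is to validate the score.

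**The concern.** Backward elimination is itself a source of overfitting. Variables survive partly because their coefficients happened to be large in this sample. A bootstrap that starts from the surviving variables and only refits their coefficients cannot see that part of the optimism. A shrinkage rule that depends on such a bootstrap therefore depends on a check that tends to look reassuring.

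The stated sequence has two weak exits. If overfitting is not flagged, an unshrunk score is published. If it is flagged, a Lasso or Ridge model replaces the one that was bootstrapped. Step 4 then describes the new model with R² and a calibration plot which, on the development data and without correction, are apparent performance.

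An unshrunk score spreads its predictions too widely. It predicts too much fluid for fast reaccumulators and too little for slow ones. These are the two groups that the score is meant to separate, and developing it is the primary objective.

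**Working it through.** **1. Reproducing the plan's shrinkage factor.** Inputs from the sample-size paragraph: n = 150, p = 8, R² = 0.5.

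Apparent R² = (R²·(n − p − 1) + p)/(n − 1) = (0.5 × 141 + 8)/149 = 0.527.

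S = 1 + (p − 2)/(n·ln(1 − apparent R²)) = 1 + 6/(150 × ln 0.473) = 0.9465, which rounds to the stated 0.95.

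The same formula under other inputs:

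| Parameters | R² 0.5 | R² 0.3 | R² 0.2 |
|---|---|---|---|
| 8 | 0.947 | 0.903 | 0.856 |
| 29 | 0.802 | 0.686 | 0.591 |

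The stated 0.95 is correct on its own terms. It applies to eight pre-specified parameters, and with eight it stays at or above 0.9 only if R² is at least about 0.30.

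**2. Number of candidates.** The Objectives section lists 10 patient items (counting the two unnumbered ones), 7 effusion, 5 pleural fluid and 7 serum items: 10 + 7 + 5 + 7 = 29. Manometry is a 20-patient substudy and would drop out. Type of malignancy, septation grade and the co-morbidities may each need more than one parameter.

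**3. Does the bootstrap detect the overfitting?** This was checked by simulation. Assumptions: n = 150, pairwise predictor correlation 0.2, five real predictors of graded strength, backward elimination at p < 0.05. With 8 candidates there were 100 data sets of 60 resamples; with 30 there were 50 data sets of 30. An issue was taken to mean a bootstrap slope below 0.9. The outline gives no value, so this was borrowed from the sample-size benchmark ("which is above the recommended 0.9").

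| Candidates | R² | Mean true slope | True slope < 0.9 | Mean slope, model held fixed | Fires, fixed | Mean slope, selection repeated | Fires, repeated |
|---|---|---|---|---|---|---|---|
| 8 | 0.5 | 0.97 | 20% | 0.99 | 0% | 0.97 | 0% |
| 8 | 0.3 | 0.92 | 42% | 0.98 | 0% | 0.92 | 17% |
| 8 | 0.2 | 0.87 | 62% | 0.98 | 2% | 0.88 | 60% |
| 30 | 0.5 | 0.92 | 44% | 0.98 | 0% | 0.89 | 74% |
| 30 | 0.3 | 0.80 | 84% | 0.97 | 2% | 0.79 | 100% |
| 30 | 0.2 | 0.71 | 90% | 0.96 | 6% | 0.71 | 100% |

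Repeating the selection recovers the true slope closely; holding the model fixed does not. Further runs with 29 candidates agree: true slope about 0.91, 0.81 and 0.68 at R² 0.5, 0.3 and 0.2, against about 0.95 to 0.97 from the fixed-model bootstrap. Across runs with eight candidates the true slope was 0.95 to 0.99 at R² 0.5 and 0.82 to 0.93 at R² 0.2 to 0.3.

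**4. What a slope means for a patient.** Take the plan's assumed mean of 14 and SD of 13, and a patient predicted one SD above the mean, at 14 + 13 = 27. The expected outcome is 14 + slope × 13:

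- slope 0.91: 25.8
- slope 0.81: 24.5
- slope 0.68: 22.8

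A patient predicted at 14 − 13 = 1 would on average reach 14 − 0.81 × 13 = 3.5 at slope 0.81.

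**5. Can Phase 2 stand in for internal validation?** At the plan's own ratio of complete to recruited patients, 40 × 150/200 = 30 are analysable. The approximate standard error of the calibration slope is slope × √((1 − R²)/(R²·(n − 2))).

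- R² 0.45, slope 0.9: 0.9 × √(0.55/(0.45 × 28)) = 0.19
- R² 0.2, slope 0.8: 0.8 × √(0.8/(0.2 × 28)) = 0.30

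The 95% interval is therefore roughly ±0.4 to ±0.6, too wide to tell 0.8 from 1.0.

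**The case against.** Several stronger readings are tempting, and the article does not support them.

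- **The trigger will almost never fire.** This holds only if the bootstrap keeps the selected model fixed. The order of steps suggests that but does not say it. With selection repeated and 30 candidates, a 0.9 trigger fires in 74 to 100% of data sets. The threshold itself is an assumption.
- **The published score would never be validated.** Phase 2 exists to validate it, and step 4 examines the final model. What is absent is a stated optimism correction for a penalised refit.
- **Penalising after elimination cannot undo the selection.** The outline does not restrict Lasso or Ridge to the surviving variables; a refit on the screened list is at least as natural a reading.
- **Overfitting is certain because there are 29 candidates.** The plan foresees reduction to eight. That step is conditional, and the outline loosens the target to a reasonable amount, so both cases have to be shown.

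Two broader objections also carry weight. Fitting, estimating optimism and then shrinking is a coherent sequence, and starting with penalised regression is a matter of choice. Bootstrap scope and trigger value are also details that a condensed article may leave to its analysis plan, so their absence alone is no finding. What stands is the sequence that the article does state: shrinkage is optional, it follows a check placed after selection, and the reported performance is not tied to the optimism estimate of the model finally published.

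**Conclusion.** The point holds in limited form and deserves a change. Following steps 3 and 4 as ordered tends to lead either to an unshrunk score or to apparent performance of a refitted one.

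The size depends on two unknowns. With about 29 candidates entering elimination, the true slope is about 0.91 at the protocol's R² of 0.5 and 0.81 to 0.68 at R² 0.3 to 0.2, while a fixed-model bootstrap would report about 0.95 to 0.97. With eight candidates the problem is small at R² 0.5 and moderate at R² 0.2 to 0.3.

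The gain in predictive R² from penalising is negligible if R² really is 0.5. In one simulation with 29 candidates, eight of them real, new-patient R² was 0.40 to 0.41 unpenalised and 0.41 penalised. At R² 0.3 the same comparison gave 0.16 to 0.17 against 0.213, with Ridge keeping all candidates, which is not a short score. The firmer benefit is honest calibration and honest reported performance.

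The R² values below 0.5, the elimination threshold, the predictor correlation and effect pattern, and the 0.9 trigger are all assumptions, so the percentages are indicative. Their direction agreed across simulations with different settings.

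**What to change.** Reword steps 3 and 4 as follows.

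1. Repeat every data-driven step in each bootstrap sample: data reduction, backward elimination, choice of splines and any penalty tuning.
2. Shrink by default, with no trigger. Multiply the selected model's coefficients by the calibration slope from that bootstrap and re-estimate the intercept.
3. Report optimism-corrected R² and calibration for the model that is published. If Lasso or Ridge is used, rerun the bootstrap on that model.

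Penalised regression on the full screened list, tuned inside each resample, is an acceptable alternative but not a requirement.

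The cost is wording and a little computing time; no extra patients or data are needed. Coefficients will be pulled towards zero and the reported R² will look less favourable. If the signal is as strong as R² 0.5 with eight variables, the shrinkage applied will be slight, so making it routine costs little.

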**Procedure for accounting for missing, unused, and spurious data**
*

Rates of missing data will be reported. For the purposes of this exploratory study, if a patient is “lost to follow-up” or dies before the three-month outcome point, it will be assumed (unless hospital records indicate otherwise) that no further pleural procedure has occurred.

*

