### Objectives and outcome measures

The primary objective of this study is
**t**o identify candidate biomarkers associated with the rate of pleural fluid accumulation in patients with MPE and to use these biomarkers to develop and validate a clinical score to predict rate of reaccumulation. These biomarkers will be measured at day 0. This will be compared with the rate of pleural fluid accumulation based on increased size of pleural effusion from CXR immediately post-aspiration to day 7
^
12
^.

*Complete list of candidate biomarkers to be assessed for the primary objective*

The candidate biomarkers include:

Patient biomarkers: i) duration of symptoms; type of malignancy; ii) known malignancy or first presentation; iii) severity of pre-procedure breathlessness (measured on visual analogue scale); iv) previous chemotherapy and/or radiotherapy and/or immunotherapy; v) current chemotherapy and/or radiotherapy and/or immunotherapy; vi) current use of diuretics; emergency (
*via* Accident and Emergency (A&E) or acute medical unit) or urgent presentation (
*via* General Practice (GP) or oncology); vii) performance status (assessed using Eastern Co-operative Group scale); and viii) co-morbidities (chronic renal failure, liver disease, cardiac failure).Effusion biomarkers: i) size of effusion on pre-procedure CXR (measured as percentage opacification of hemithorax - this is a validated measure of effusion size); ii) size of effusion on pre-procedure US (measured from hemidiaphragm to top of effusion); iii) side of effusion; iv) volume of fluid drained during therapeutic aspiration (ml); v) degree of pleural fluid septations (categorised as none, mild, moderate or severe) on US; vi) significant non-expandable lung on post-procedure CXR; and vii) pleural pressures measured by manometry (substudy in 20 patients only in Norwich).Pleural fluid biomarkers: i) total protein; ii) pH; iii) glucose; iv) lactose dehydrogenase (LDH); and v) cytology (categorised as positive
*i.e.*, malignant cells present or negative).Serum biomarkers: i) haemoglobin; ii) white cell count, including neutrophil and leukocyte subsets; iii) C reactive protein; iv) total protein; v) estimated glomerular filtration rate (eGFR); vi) LDH; and vii) N-terminal pro-brain natriuretic peptide (NT-proBNP).

**
*Why were these biomarkers chosen?*
**

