### Follow-up visits

**Day seven:** follow-up visit seven days after the therapeutic aspiration (can be done 5–10 days). This is part of standard clinical care for patients to receive results of pleural fluid testing and decide a management plan. Patients standardly have a CXR at this visit and this will be used to reassess size of effusion. At the point, the 7DVQ will be collected and a CRF completed, particularly to assess whether participants have required further pleural fluid drainage or attended the hospital with breathlessness during the seven-day period. During this period the participant is permitted to have any clinically required intervention.
**Second pleural procedure:** this will be performed if clinically indicated for diagnostic or symptomatic reasons. Indications for symptomatic drainage are as follows: symptomatic benefit from initial pleural fluid drainage; significant breathlessness; and significant pleural effusion (defined as at least 25% of the hemithorax on CXR or estimated volume of pleural fluid of at least 500 ml using US). Participants will undergo a further pleural drainage (
*via* thoracoscopy, chest drain or indwelling pleural catheter insertion according to clinical requirement in their individual care pathway). Patients will undergo CXR and US at this visit prior to intervention.
**Day 30:** follow-up by telephone/review of hospital records to determine further pleural procedures, emergency hospital attendances, other treatment for effusion
*e.g.*, chemotherapy, surgery, diuretics.
**Three months:** follow-up by telephone/review of hospital records to determine further pleural procedures, emergency hospital attendances, other treatment for effusion
*e.g.*, chemotherapy, surgery, diuretics. We will also collect health related QoL data using the EQ-5D 5L questionnaire by telephone.

Research staff will informally assess capacity at each follow-up visit. If the investigator believes that the participant has lost capacity to consent, no further data will be collected, and they will be withdrawn. The study data and samples will be used/retained if the participant had consented for this during the initial consent process.

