**Inclusion in analysis**
*

All participants with available data will be included in the day seven analysis. For the one month and three-month outcomes, all participants including those lost to follow-up or who die within the time period will be included in analysis.

*

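### Counting patients lost to follow-up as having had no further pleural procedure can only bias the one-month and three-month procedure proportions downward

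*Protocol article*

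**What the plan says.** The rule is in the protocol article under 'Procedure for accounting for missing, unused, and spurious data'. For a patient who is lost to follow-up, or who "dies before the three-month outcome point, it will be assumed (unless hospital records indicate otherwise) that no further pleural procedure has occurred". The sentence describes the study as exploratory.

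'Inclusion in analysis' fixes the denominator: "For the one month and three-month outcomes, all participants including those lost to follow-up or who die within the time period will be included". The rule itself is worded for three months. Because the same patients are kept at one month, the same coding presumably applies there.

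'Follow-up visits' gives the means of ascertainment at day 30 and three months: "follow-up by telephone/review of hospital records to determine further pleural procedures, emergency hospital attendances, other treatment for effusion". For a participant who loses capacity, the same section says that "no further data will be collected, and they will be withdrawn". Neither section says how such a participant is coded for the later outcomes.

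The score rests on another outcome, described in 'Objectives and outcome measures' as the "rate of pleural fluid accumulation based on increased size of pleural effusion from CXR immediately post-aspiration to day 7". 'Sample size and analysis plan' confirms the timing: "The primary outcome measure is at one week and is part of standard clinical care".

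**The concern.** Loss to follow-up means that observation stopped. It is not evidence that the patient went on to three months without a procedure. The rule fills the gap with a single value, and always the same one. If the patient had a procedure that the records do not show, for example at another hospital, it is removed from the numerator while the patient stays in the denominator. No error in the opposite direction can offset it.

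The rule also gives one code to three different histories: alive at three months with no procedure, dead without a procedure, and unknown. The study wants to identify patients whose fluid returns slowly or not at all, and only the first history is evidence of that.

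At stake are the later procedure proportions, which describe current practice. They could also carry into the planning of Phase 3, where the number of pleural procedures is an outcome.

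**Working it through.** **The plan's own figures.** The article states no expected procedure proportion, death rate or loss rate at three months for this study. Its sample-size figures (150 patients, 8 parameters, R² of 0.5) concern the day-7 model, and none of them depends on this rule.

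**Inputs.**
- True three-month proportion: 48%, assumed. The scale comes from the retrospective cohort described under 'Review of existing evidence', where 52% had no further procedure at 90 days: 100% − 52% = 48%. The article does not say how deaths and losses were handled in that cohort, so 48% is only an anchor.
- Share lost, L: not given; 2% to 20% assumed.
- Share of the lost patients' procedures that do not reach the records, m: not given; 0.5 and 1 assumed.
- Lost patients are taken to have the same true proportion as the others.

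**Losses.** Recorded proportion = 0.48 × (1 − L × m).

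| Lost | None seen (m = 1) | Half seen (m = 0.5) |
|---|---|---|
| 2% | 47.0% | 47.5% |
| 5% | 45.6% | 46.8% |
| 10% | 43.2% | 45.6% |
| 20% | 38.4% | 43.2% |

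In counts, for 150 patients: 150 × 0.48 = 72 would have a procedure. With 10% lost, 15 patients are lost and 15 × 0.48 = 7.2 of the procedures are theirs. If none is seen, the record shows 64.8/150 = 43.2%. If records catch every procedure, m = 0 and there is no bias.

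**Deaths.** Suppose nobody is lost, and of N patients e have a procedure and d die without one. The rule reports e/N. The Aalen-Johansen cumulative incidence with death as a competing event, with no censoring, is also e/N. The rule and the preferred estimator therefore agree for deaths, provided that procedures before death are recorded.

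The crude proportion is lower only than a hypothetical risk in the absence of death. With constant hazards over 90 days, write a = −ln(0.52) = 0.654 for procedures and b = −ln(1 − D) for 90-day mortality D. The cumulative incidence is a/(a + b) × (1 − e^−(a+b)). For D = 20%, b = 0.223, giving 0.654/0.877 × (1 − 0.52 × 0.80) = 43.5%. For D = 40% it is 38.6%. These are the cumulative incidences themselves and not distortions of them.

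**Biomarkers, conditionally.** In the same model, take a marker that doubles the death hazard and has no effect on the procedure hazard. At 20% baseline mortality the proportion with a procedure falls from 43.5% to 39.7%, a risk ratio of 0.91. Across 10% to 40% mortality the ratio runs from 0.96 to 0.82, and for a marker that triples the death hazard from 0.91 to 0.69. This matters only if biomarkers are related to a yes/no three-month procedure outcome, and the article describes no such analysis.

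**Limit of the illustration.** A constant hazard that reaches 48% at 90 days implies 1 − 0.52^(15/90) = 10% by day 15, whereas the cited cohort had 30%. The calculations for deaths and biomarkers therefore show direction and rough scale only.

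**The case against.** The strongest defence is the exception for hospital records. Record review is one of the planned routes to the later outcomes, and a further drainage procedure would ordinarily appear there. Only procedures missing from the records are miscounted, and the article expects little loss, although it says so of the one-week outcome. This defence stands and it limits the size. It does not remove the direction of the bias, and it cannot help where data collection has stopped.

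It can also be said that the rule is labelled exploratory, that the outcomes are later ones, and that time-to-event detail is often left to an analysis plan. But the article does not leave this open: it states a coding rule and a denominator.

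Two stronger readings are tempting. A reader might infer that counting deaths as no procedure understates the procedure rate. It does not, if the target is the cumulative incidence with death as a competing event: a patient who died without a procedure had none. The article names no death-free risk as its target.

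A reader might also infer that markers of early death will look protective in the score, since the article says that "LDH has been identified as a variable associated with poor prognosis in patients with MPE" and makes a similar statement about haemoglobin, the neutrophil ratio and C reactive protein. The score is built on X-ray change to day 7, analysed in participants with available data, so this rule never enters it.

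Finally, the missing-data section names loss and death only. Applying the rule to withdrawal for loss of capacity is an inference, because the article does not say how those participants are coded.

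**Conclusion.** The concern holds for patients lost to follow-up. Coding them as having had no further procedure, and keeping them in the denominator, can bias the one-month and three-month procedure proportions only downward. The size cannot be fixed from the article. Against an assumed true 48%, it is 2.4 percentage points at 5% lost and 4.8 points at 10% lost if none of their procedures are seen, and 2.4 points at 10% lost if half are seen. It is nil if the records are complete.

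For deaths the proportion is right as a cumulative incidence. What needs changing is the presentation: death should be reported as a competing event, so that an early death is not taken as slow reaccumulation. The day-7 score and its sample size are untouched. An apparent protective effect of markers of early death would arise only if biomarkers were related to the three-month procedure outcome. This is a modest point about later outcomes.

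**What to change.** Replace the assumption of no further procedure with time from aspiration to the next pleural procedure:

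- Censor patients lost to follow-up at the last contact or last record check, whichever is later. Do the same for participants withdrawn with no further data collected, and state this explicitly.
- Treat death without a procedure as a competing event, and report the Aalen-Johansen cumulative incidence of procedure and of death at 30 days and three months.
- Use cause-specific hazard models for any predictor analysis of this outcome.
- Keep the present rule as a sensitivity analysis only. Censoring assumes that loss is unrelated to the chance of a procedure, which is doubtful where loss follows disease progression. The present rule shows the result if no lost patient had an unrecorded procedure.

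The cost is small: revised wording, some extra analysis, and recording the dates of procedure, death and last contact or record check. Most of this can come from the planned telephone and record follow-up.
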